## Abstract

**Methods and analysis::**

For this purpose, individuals who have been diagnosed with COVID-19 and have had a tension headache and/or orofacial pain for more than 3 months will be selected by convenience. The participants will be divided into two different groups: G1-photobiomodulation with red and infrared laser with local application on the pain points (808 nm and 660 nm, 100 mW, 6 J per point) and G2-photobiomodulation with red laser with transcutaneous application on the radial artery (660 nm, 100 mW, 30 minutes). All participants will be treated for a period of 4 weeks, with 8 application sessions. The effects will be measured by means of blood lactate level, Brief Pain Inventory, Visual Analog Scale (VAS), and Cephalea Impact Test. The data will be collected weekly before and after the treatment, and the following tests will be applied: Analysis of variance (ANOVA), Tukey paired *t* test, Kruskal–Wallis, or Wilcoxon, according to data distribution. α = 0.05 will be considered as the level of statistical significance.

**Ethics and dissemination::**

This study was approved by the Research Projects Committee of the Nove de Julho University (approval number 4.673.963). Results will be disseminated through peer-reviewed journals and events for the scientific and clinical community, and the general public. It is registered in the ClinicalTrials.gov database with the number NCT05430776.

Strengths and limitations of this studyThis study is an assessment for treatment for health impacts of the pandemic. This is a pragmatic study. Lasertherapy can be a non- invasive proposal for the treatment of pain resulting from COVID-19. There is not enough information in the literature on the relationship between laser therapy and post-covid-19 pain-related sequelae.

## 1. Introduction

Orofacial pain is defined as pain associated with tissues (skin, blood vessels, bones, teeth, glands, or muscles) of the oral cavity and face. Often, this pain can be referred to the head and/or neck region or even associated with cervicalgia, primary headaches, and rheumatic diseases.^[1,2]^

Cephalea refers to any referred pain in the cephalic segment and is a very common manifestation. During life, the prevalence of cephalea is higher than 90%, representing the third most common occurrence (10.3%) in neurology outpatient clinics. Cephalea is considered a public health problem, as they are debilitating disorders that sometimes make routine actions impossible, which causes a great personal and social impact.^[3,4]^

According to the International Classification of Cephalea, there are five predominant types of primary Cephalea, the most common being tension-type cephalea (TTH).^[3]^ This kind of pain is described as a pressure with mild to moderate intensity, bilateral.^[5]^

TTH is the most prevalent type worldwide, and the stiffness in the myofascial tissue in the cervical and cranial region strongly connects with the frequency and intensity of the discomfort. Genetic, emotional, and peripheral factors, such as nociception and central factors (central sensitization), are noted as etiological for orofacial pain.^[6]^

In addition to tension headache, temporomandibular disorders (TMD) are related to orofacial pain with signs and symptoms that include joint noises, limitations in range of motion or deviations during mandibular function, and temporomandibular joint pain.^[7,8]^

In 2020, the world was surprised by the pandemic of COVID-19, a disease caused by the coronavirus (SARS-CoV-2). The disease affected millions of people, causing many deaths. The clinical course of this new infection is characterized by respiratory symptoms and complications, however, cephalea is one of the signs frequently reported by COVID-19 patients.^[9]^

The cephalea attributed to the current viral infection is known as migraine or TTH, according to the 3rd edition of the International Classification of Headaches.^[10]^

It is estimated that with the pandemic COVID-19 there has been a 5-fold increase in the incidence of cephalea, and the most frequent pattern is bilateral. Other conditions were also evaluated the duration, frequency, course of the pain, and the relationship with a possible post-COVID-19 syndrome, as the disease has potential medium and long-term consequences.^[11]^

The worsening of the psycho-emotional state during the pandemic contributed not only to the increased incidence of cephalea but also to TMD-related pain.^[12,13]^

The importance of psychosocial factors in the development and maintenance of TMD is well established, and these factors have become more threatening to orofacial pain during the pandemic.^[14]^ However, in addition to psychosocial factors, the involvement of facial sensory innervation such as olfaction and taste. Although independent structures, there is an interrelationship between the olfactory nerve and the trigeminal nerve, contributing to the development and prolongation of orofacial pain.^[15]^

The recommended treatment for orofacial pain, as well as for cephalea, in general, aims at reducing the pain symptom and recovering the function. Pain control is often accomplished with the prescription of analgesics, anti-inflammatories, and other types of auxiliary drugs. However, in post-COVID-19 patients, pharmacological treatment may result in drug interactions resulting from the treatment for the viral infection. Considering this, the non-pharmacological auxiliary options that have the potential to contribute to pain relief can be considered.

One of the auxiliary treatment options for analgesia in TTH and TMD orofacial pain is photobiomodulation, that is, the use of a low-intensity laser or even light-emitting diode.

Low-intensity laser therapy (LILT) is being used frequently as a therapeutic procedure in a variety of medical situations, such as edema and inflammation control, chronic joint disorders, pain, and wound healing, among others.^[16–20]^

Chronic cephalea and cephalea associated with TMD have benefited from photobiomodulation for pain control. Therapeutic effects of LILT in TMD and headaches include an inflammatory modulator and analgesic effects.^[21–24]^ LILTs have demonstrated the ability to aid in the symptomatic treatment of pain, providing a considerable degree of comfort to patients right after their application. One of the main advantages of LILT is that it is a noninvasive, low-cost pain relief therapy. The use of laser therapy in patients with facial pain showed pain relief within minutes after its application, providing a significant well-being state. It is an auxiliary treatment for pain relief due to the analgesic action of the laser that allows the patient to resume their activities, providing more comfort and a better quality of life.^[21,22,24–26]^

Considering the auxiliary potential effect of photobiomodulation in controlling persistent TTH and TMD-related pain in patients who have been diagnosed with COVID-19, and are recovered from the viral infection, we intend to conduct a clinical trial comparing two modalities of therapeutic laser application: local application and transcutaneous application in the radial artery.

One of the main advantages of auxiliary techniques in pain control is the decrease of the use of drugs for analgesia, avoiding side effects and tolerance caused by them, and promoting an improvement in the individual’s quality of life.

## 2. Method

This is a pragmatic, randomized, parallel, single-blind clinical trial. The design follows the international recommendations for randomized clinical trials that are displayed in the SPIRIT Statement (Standard Protocol Items: Recommendations for Interventional Trials).

The research follows the regulatory norms established for human subjects research by the Research Ethics Committee of the Nove de Julho University with approval under number 4.673.963 that will periodically monitor the conduct of the study through semiannual reports. This is a low-risk study and symptom relief assessment does not require DMC. The participants will sign the free consent form after clarification, according to resolution 466/12 of the National Health Council. The recruitment procedures, eligibility assessment, and treatment will be carried out at UNINOVE’s Integrated Health Outpatient Clinics.

The selected subject will be individuals from the ages of 18 to 65 years, of both sexes, who have been diagnosed with COVID-19, confirmed by RT-PCR for SARS-CoV-2 already recovered at least 30 days from the infection, and present with orofacial pain will be selected.

Since this is a new scenario in health care and the information on the participants’ conditions is very recent, we chose a convenience sampling design. Considering a prevalence of persistent orofacial pain in infected participants of 11%,^[11]^ with a margin of error of 5%, reliability of 95%, and power of 80%, we intend to recruit, at least, 40 participants.

Participants will be invited to participate in the selection criteria that will follow the routine anamnesis and diagnosis of the International Classification of Headache and orofacial pain questionnaire.

### 2.1. Inclusion criteria

-Individuals of both sexes, between the ages of 19 and 65, complaining of persistent orofacial pain or functional-type cephalea, for more than 3 months.-Individuals diagnosed with COVID-19, confirmed by RT-PCR for SARS-CoV-2 already recovered, at least 30 days after infection.

### 2.2. Exclusion criteria

-Individuals with diagnoses of neuropathies and headaches other than tension-type headache-Physical or intellectual incapacity to answer the survey questionnaires; illiterate; diabetics, pacemakers, and pregnant women.-Individuals who report photosensitivity to laser.

### 2.3. Discontinuation criteria

Participants who report any discomfort during the protocols, who present sensitivity to the laser application, or who do not attend more than two appointments in a row will be discontinued and the data will be computed for further analysis.

### 2.4. Study variables

Sociodemographic information will be collected, such as age, self-reported skin color, education, occupation, weight, height, and practice of physical activity. Besides the sociodemographic information, clinical information will be collected, such as the history of systemic diseases and personal and family history of health problems, treatments performed previously and at the time of the survey, and medications used.

### 2.6. Blood lactate level

For blood collection, a disposable and sterile lancet will be used. A small prick will be made on the right earlobe, and the collected blood (25 µL) will be deposited on a reactive tape to be analyzed in a portable lactometer (Detect TD-4261 Lactate Analyzer, EcoDiagnóstica, MG/Brazil, [contact]). The lactate level will be collected once a week, before and after the application of the protocol. The lactate level is related to muscle activity and may help in the understanding of the effect of photobiomodulation in this research.

The need for medication changes or the introduction of new drugs other than the usual ones will also be collected by means of a medication recall.

### 2.7. Research conduct and protocol

The treatment will be carried out in 8 weeks (2 sessions per week) with an average duration of 60 minutes per session. At the end of the 8-week treatment, a new evaluation will be performed after 1 month of follow-up.

After selection, the participants will be randomized into two groups: (G1) photobiomodulation with red and infrared laser with local application on pain points and (G2) photobiomodulation with red laser with transcutaneous application in the radial artery.

The draw for allocation to the groups will be carried out by means of generating number sequences on the electronic platform www.randon.org. The sequence will be kept in a sealed opaque envelope. Only one researcher will have access to the sequencing.

After allocation, the participants will answer the evaluation scales and the blood will be collected for analysis of the initial lactate level (Fig. 1).

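### Allocation concealment is not secured: the whole sequence sits in one envelope open to one researcher of unstated role, and baseline is measured after allocation

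*Protocol article*

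**What the plan says.** Section 2.7 (Research conduct and protocol) covers generation, concealment and timing in a few lines.

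- Generation: "The draw for allocation to the groups will be carried out by means of generating number sequences on the electronic platform".
- Concealment and access: "The sequence will be kept in a sealed opaque envelope. Only one researcher will have access to the sequencing".
- Entry: "After selection, the participants will be randomized into two groups".
- Baseline: "After allocation, the participants will answer the evaluation scales and the blood will be collected", the blood being for the initial lactate value.

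Section 2 (Method) adds that "we chose a convenience sampling design" and that "we intend to recruit, at least, 40 participants". It calls the trial single-blind without naming who is blinded. It places recruitment, eligibility assessment and treatment at one institution's outpatient clinics.

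The article mentions no numbered envelopes, no envelope per participant and no central or one-at-a-time release. It does not say what else the researcher with access to the sequence does in the trial.

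**The concern.** A sealed envelope holding a complete list conceals that list only until it is first opened. If participants are allocated as they enter, the list must be consulted repeatedly, and after the first consultation the seal protects nothing. What then keeps the next assignment hidden from those who enrol is the conduct and independence of the one person with access, and the article is silent on both.

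Four features of this trial make that matter.

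- Sampling is by convenience, which leaves room over whom to approach and when.
- Some eligibility decisions need judgement, notably the type of headache and the exclusion of neuropathies (sections 2.1 and 2.2).
- The arms look different to anyone present: points on the face and neck in one, a wristband over the radial artery in the other. Blinding is therefore a weak backstop.
- The pain and headache-impact outcomes are self-reported.

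If the next arm were known at enrolment, entry could be timed or steered by it. The tests in section 2.8 cannot reliably remove imbalance on unmeasured characteristics.

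The baseline order raises a related problem. Once a participant or assessor may know the arm, the baseline pain score is no longer guaranteed to be a pre-treatment measure independent of assignment.

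**Working it through.** The plan gives no figure to reproduce. The check is a reading of the text plus one count.

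**1. What the first opening exposes.** Inputs: one sequence and one envelope (section 2.7); n of at least 40 (section 2).

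- One list in one envelope: assignments exposed beyond the one needed = n − 1 = 40 − 1 = 39, or more if more than 40 are recruited.
- One sealed envelope per participant, or release one at a time: 0 exposed.

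**2. To whom they are exposed.** The access sentence limits this to one researcher. The consequence depends on that person's other duties:

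| Holder of the list | Next assignment hidden from those who enrol? |
|---|---|
| No role in recruitment, assessment or treatment; releases one at a time | Yes, even with a single list |
| Also recruits or judges eligibility | No, from the second participant on |
| Has another role but passes assignments on | No, for whatever is passed on |

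The article does not say which row applies. Only the first secures concealment.

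**3. Order of events.** Setting the entry and baseline sentences side by side gives: selection, then allocation, then baseline scales and lactate. For each participant, selection comes before that participant's own assignment is applied. This does not stop a list holder who also recruits from already knowing what the assignment will be.

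**4. What the order does to baseline.** Section 2.8 compares study periods with paired t or Wilcoxon tests. Suppose the baseline evaluation is one of the periods compared, and knowledge of the arm shifts a baseline score by b. Then:

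observed change = follow-up − (true baseline + b) = true change − b.

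The whole shift passes into the change score. If b differs between arms, so does the artefact. The documents give no basis for a value of b, so none is assumed.

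**The case against.** The strongest reply is that access is restricted. Opening the envelope informs one researcher and not the recruiting team, and a sole custodian who releases assignments singly would keep recruiters unaware even with one list. This stands. A reader might infer from the text that concealment is lost from the second participant on, or that selection bias is present. The article supports neither, because it never says that the custodian recruits, assesses or treats, or shares the list.

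A second reply is that a journal article may leave envelope numbering and staff roles to the full protocol. This is partly right: silence on roles alone would not be a finding. But the article states a mechanism, a single envelope for the whole sequence, and that mechanism is inadequate after its first use unless something unstated supports it. The singular may be loose wording for one envelope each. Nothing in the text points that way, and if it was meant, the correction is a clarification.

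A third reply is that discretion at entry is narrower than it seems, since PCR confirmation, time since infection, pain duration and age are fixed criteria and headache diagnosis follows a named classification. This too stands in part. Judgement remains on pain type, and convenience sampling leaves choice over whom to approach. Convenience sampling is not itself evidence that recruiters know the allocations.

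Finally, 39 of 40 should not be taken as the size of a bias. It is the minimum sample less one and says nothing about magnitude or direction.

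**Conclusion.** The point holds as a weakness in how concealment is fixed. As written, the first opening exposes all later assignments, at least 39, to one researcher whose independence from recruitment, assessment and treatment is not stated. Concealment is therefore not secured, and baseline self-reports are collected when the arm may already be known. Bias is possible but not demonstrated, and its size cannot be estimated from the article.

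This rests on three assumptions:

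- The singular envelope is meant literally.
- Participants are allocated as they enter. If everyone were selected before the envelope was opened, steering of entry would not arise, but the article does not say so.
- No fuller document separates the custodian's role.

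The baseline-order point does not depend on any of these, since the sequence is stated outright. What it does depend on is whether the arm is known to the participant or assessor at that moment, which the article leaves open.

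The change should be made before enrolment, because concealment cannot be restored afterwards.

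**What to change.** Amend two sentences in section 2.7.

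1. Replace the envelope sentence with one stating that assignments are held in sequentially numbered, individually sealed opaque envelopes, one per participant, or are released one at a time by a custodian. The holder should be an existing team member with no role in recruitment, assessment or treatment. Each assignment is opened or released only after eligibility is confirmed and baseline scales and lactate are recorded.
2. Reverse the order in the sentence that now puts the scales and blood sample after allocation. Changing only the envelope sentence would leave the section contradicting itself. The Figure 1 schedule, which was not available to check, should be aligned if it shows the present order.

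The cost is about 40 envelopes (more if recruitment passes the minimum), two amended sentences and a small change in visit order. It assumes that the team has someone outside recruitment, assessment and treatment who can hold the list; the article does not describe staffing. Sample size, outcomes and analysis are unaffected.

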**Figure 1. F1:**
[figure not shown]
Schedule of enrollment, interventions, and assessments. This clinical trial will follow the consort (Consolidated Standards of Reporting Trials) recommendations. Figure 1 presents the flow chart of the research. BPI = Brief Pain Inventory, HIT-6 = Headache Impact Test, VAS = Visual Analog Scale.

The participants will be positioned on a clinical chair or stretcher for the application of photobiomodulation at the Universidade Nove de Julho dental clinic. The interventions will be performed by trained professionals.

G1 will receive the application of photobiomodulation with the device The Ecco Reability (Eccofibras, São Paulo, Brazil) containing its infrared wavelength of 808 ± 10 nm and red 660 ± 10 nm concomitant and power 100 mW, properly calibrated and energy of 6 J per point (60 seconds) in 8 points, 2 sessions per week in 8 points on the face and neck. The points will be those referred to by the participant as pain or trigger points located during the clinical examination. G2 will receive the application of photobiomodulation with the device The Ecco Reability (Eccofibras) containing its red wavelength 660 ± 10 nm concomitant and power of 100 mW, with an application time of 30 minutes (Table 1).

**Table 1 T1:** Dosimetric parameters of photobiomodulation application.

Parameters	Red laser (Local)	Red laser (Local)	Red laser (systemic transcutaneous)
Wavelength (nm)	808	660	660
Operation mode	Continuous	Continuous	Continuous
Power (mW)	100	100	100
Opening diameter (cm)	0.354 (beam diameter with spacer)	0.354 (beam diameter with spacer)	
Beam area (cm^2^)	0.0984 (with spacer)	0.0984 (with spacer)	
Exposure time (s)	60 per point	60 per point	1800
Fluency (J/cm^2^)	61	61	–
Energy (J)	6 per point	6 per point	180J
Number of irradiated points	8	8	Systemic
Application technique	Contact	Contact	Contact
Session number	8	8	8
Treatment frequency	2 times a week	2 times a week	2 times a week
Total energy radiated (J)	384 J	384 J	1440 J

The device will be positioned with the spot located on the radial artery of the participant’s preferred arm (right or left) and attached to the wrist with a specific wristband. There will be 8 transcutaneous applications, 2 sessions per week of 30 minutes each session.

Any changes made to the protocol will be communicated to the participants using the media of Universidade Nove de Julho and the academic community involved through attachments in the original project.

### 2.8. Statistical analysis

The data will be presented descriptively as to the sociodemographic variables and clinical characteristics of the sample. The data of the clinical variables will be analyzed by statistical software SPSS 23.0 for Win. After the normality test, Analysis of variance (ANOVA) followed by Tukey’s test will be applied when necessary and for the treatment results in the study periods, the paired *t* test will be used. If the hypothesis of normality is rejected, the Kruskal–Wallis test will be used followed by Student’s test, and for comparison in the different study periods, the Wilcoxon test will be used. We will take α = 0.05 as the level of statistical significance.

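### A normality test on the trial data decides whether each scale is tested on means or on ranks, so the tested quantity is not fixed in advance

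*Protocol article*

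**What the plan says.** Section 2.8 sets out two branches. In the mean branch, "After the normality test, Analysis of variance (ANOVA) followed by Tukey’s test will be applied when necessary", with the paired t test for results across study periods. The rank branch is triggered by the condition "If the hypothesis of normality is rejected". Between groups it then calls for Kruskal–Wallis, with a Student test as follow-up. Across periods the wording is "for comparison in the different study periods, the Wilcoxon test will be used". The abstract gives the same rule in short: tests are applied "according to data distribution".

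The normality test is not named and has no stated level. The text does not say whether it is run once per scale, once per arm or at each occasion, or whether raw scores or changes enter it. The significance level is fixed: "We will take α = 0.05 as the level of statistical significance". On size, section 2 says "we intend to recruit, at least, 40 participants", and section 2.7 says "the participants will be randomized into two groups". Under section 2.5 the VAS and the BPI items run from 0 to 10; BPI is taken weekly and VAS at the start and end of each session. Section 2.6 has lactate taken weekly.

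**The concern.** The two branches answer different questions. ANOVA and the t test compare means. Kruskal–Wallis with two groups, like the Wilcoxon rank-sum test, asks mainly whether values in one arm tend to be larger than in the other. A rule that picks between them after the data are seen leaves the compared quantity to the sample.

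At about 20 per arm a normality test has limited power and a real chance of a false alarm, so the branch depends partly on luck. The floor at 0 adds to this: as pain falls, scores pile up at the bottom and normality is rejected more often. A reader of the results could not tell in advance whether a reported p-value refers to a difference in mean pain or to a shift in rank order.

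The protocol states this rule. It is not a detail that the article has left to an unseen analysis plan.

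**Working it through.** The plan gives no figure for how its rule behaves, so there is none to reproduce. The checks below are simulations and a worked example.

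**Inputs from the protocol.** At least 40 participants (section 2), two groups (section 2.7), alpha 0.05 and the two-branch rule (section 2.8), scores from 0 to 10 (section 2.5). The allocation ratio is not stated; taking 1:1 gives 40 / 2 = 20 per arm.

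**Assumed, because the protocol is silent.** Shapiro–Wilk at 0.05 in each arm, with the rank branch entered if either arm rejects; two-sided tests. For step 2 also: 5 occasions, SD 2, correlation 0.5 between occasions, linear decline, scores cut at 0 and 10.

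**Step 1: how often the rank branch is entered on a single occasion (20 per arm).**
- Both arms truly normal: 9.8%. This is about what two 5% tests give: 1 − 0.95² = 9.75%.
- Both arms with skewness 1: 50%.
- Both arms with skewness 2: 97%.
- 0–10 score with floor, latent SD 2: 8% at latent mean 6, 59% at mean 2, 98% at mean 1.

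**Step 2: how often one scale would be tested both ways across 5 occasions, if the check is run at each occasion.**

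| Mean score over the trial | Trials using both branches |
|---|---|
| Flat at 5 | 32% |
| 5 falling to 3 | 38% |
| 5 falling to 2 | 72% |
| 5 falling to 3, whole-number scores | 79% |

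**Step 3: type I error of the two-stage rule.** With the same distribution in both arms it is 5.2% to 5.4%, so there is no material inflation.

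Now let mean change be equal and the response pattern differ. Arm A is Normal(−2, SD 1.5). Arm B is one-third strong responders, Normal(−5, 1), and two-thirds weak responders, Normal(−0.5, 1). The mean of B is (1/3)(−5) + (2/3)(−0.5) = −1.67 − 0.33 = −2.0, equal to A. Rejection rates:
- t test 4.9%
- Kruskal–Wallis used on every trial 8.8%
- two-stage rule 8.8%

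The reason lies in what ranks measure. The difference between one B value and one A value has SD √(1 + 1.5²) = 1.80 within each component. The chance that a B patient improves less than an A patient is (2/3)Φ(1.5/1.80) + (1/3)Φ(−3/1.80) = (2/3)(0.797) + (1/3)(0.048) = 0.55, not 0.50. The means are equal but the rank order is not.

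**Step 4: one worked data set, 20 per arm.** In one arm improvement is spread evenly from 1 to 3. In the other, 15 patients are spread evenly from 0 to 1.2 (mean 0.6) and 5 are at 6.2. The means are 2.0 and (15 × 0.6 + 5 × 6.2)/20 = 40/20 = 2.0. Shapiro–Wilk gives p = 0.55 and p = 0.00001, so the rank branch applies. Kruskal–Wallis gives p = 0.010; the t test gives p = 1.00.

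**The case against.** Three stronger readings are tempting, and the documents do not support them.

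- **That the stated 0.05 fails.** A reader might infer that the two-stage rule inflates the error rate in general. It does not: with a common distribution in both arms the rate stays near 5%. In the example with excess, Kruskal–Wallis alone rejects as often as the two-stage rule (8.8% each), so a fully prespecified rank test would show the same excess. The arms there really do differ in response, so rejecting equality of distributions is no error. It is an error only if the result is read as a difference in means.
- **That Kruskal–Wallis reacts to any difference in shape.** It does not. At 20 per arm it rejects in 5.2% of trials for normal against uniform and 4.7% for normal against Laplace. What matters is a difference that shifts the rank order, such as differently asymmetric responses.
- **That the test will switch from week to week.** Section 2.8 speaks of the normality test in the singular and does not say that it is repeated. It does not say that one branch is held for a scale either. The switching rates are therefore conditional, and they use a mean, SD, correlation and decline that the protocol does not give. A different path of decline would change the percentages.

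It is also fair to say that effect measures and intervals are commonly left to a fuller plan, so their absence from the article is not the point. What stands is narrower: the article itself commits to a choice of test made from the trial data.

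**Conclusion.** The point holds in limited form. Section 2.8 and the abstract let the trial data choose between a comparison of means and a comparison of ranks, so the quantity tested is not fixed beforehand for any scale. That conclusion rests on the text alone.

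Its practical size rests on assumptions. At 20 per arm (1:1 assumed), with Shapiro–Wilk at 0.05 in each arm, the branch is far from predictable at moderate skew or near the floor. If the check is repeated over 5 occasions, mixed testing of one scale occurs in about a third to four-fifths of trials; treat those figures as illustrative. The consequence for error is confined to arms with equal mean change and differently asymmetric responses, about 9% against 5% in the example, and is due to the changed hypothesis. This should be corrected, but it does not by itself invalidate the comparison of the two groups.

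**What to change.** Delete the normality check from section 2.8 and the matching phrase in the abstract, and replace it with rules that do not depend on the data:

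1. **Between groups.** For each scale, prespecify the G1–G2 difference in means at the end of treatment, from a linear model adjusted for the baseline value, with 95% CI and heteroscedasticity-robust standard errors.
2. **Sensitivity.** Report one Wilcoxon rank-sum analysis per scale whatever the distribution looks like, and state that it tests a different hypothesis.
3. **Within group.** Report mean change over periods with 95% CI (paired t) descriptively, with no normality check.

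The cost is a rewrite of the short analysis section and one phrase in the abstract; no data collection changes. The drawback is some loss of power if outcomes are strongly skewed, which the rank analysis would help to show. The end-of-treatment time point also needs one definition: the abstract gives a 4-week period and section 2.7 gives 8 weeks, and the two must be reconciled.
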